## Assignment of interventions: allocation

### Sequence generation

A statistician who is independent and separate from the research team will use the SAS (SAS Institute Inc, Cary, NC, USA) randomisation programme to generate random numbers with simple randomisation.

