### Trial design

This randomised, double-blinded, parallel, superiority trial will be completed at three research centres, including the First Affiliated Hospital of Guangzhou University of Chinese Medicine (GZUCM), Wuyi Hospital of Traditional Chinese Medicine and Dongguan People’s Hospital, over 2 years. A total of 104 patients with low simple intersphincter anal fistulas who meet the study criteria will be randomised (1:1) to the test and control groups. The intervention will last for the whole duration of the hospital stay with a follow-up of 6 months. Informed written consent will be obtained prior to the commencement of this study. All enrolled subjects will be fully informed about the purpose, process and possible risks of the study.

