## Methods: participants, interventions, and outcomes

### Study setting

The study will be completed at three research centres.

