### Sample size

This study is a superiority trial. Our pretest showed that the average wound healing times of the graft and no-graft groups were approximately 15 and 25 days, respectively. We assume that no difference in efficacy exists among the three centres. Assuming a two-sided significance level of 0. 05 and power of 80% (*α* = 0. 05, *β* = 0. 2), the sample size is calculated as 47 (fixed model as $$n_{1} = n_{2} = \frac{{\sigma^{2} \left( {{\text{t}}_{\alpha } + t_{\beta } } \right)^{2} }}{{\delta^{2} }}$$) [11]. Considering a loss to follow-up of 10%, the sample size for each group is 52 cases, and the total is 104 cases.

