### Recruitment

This RCT, in which assessors and patients are blinded, will be conducted at three research centres. The subjects in this study will be recruited from outpatient and inpatient wards by placing advertisements on social media platforms and distributing posters with details of the study and contact information in public areas of hospitals.

Patients who meet the inclusion criteria will be invited to participate in the study and provided with the details of the RCT protocol. All patients will be required to sign an informed consent form and provide complete information. The patients will be randomised (1:1) to the test and control groups. None of the patients will know about their assigned group to keep the trial blind. Then, their baseline characteristics will be assessed, and a database record will be obtained by the same colorectal surgeon. All patients will be treated with surgery and followed up on the 3rd day, 7th day, 14th day, 21st day, 28th day, 2nd month, 3rd month and 6th month postoperation. After follow-up, pictures of the wounds will be taken, and data will be evaluated.

In addition, all of the patients will be given a schedule of intervention dates and follow-up appointments. These evaluations will be performed by an assistant who will be involved neither in the randomisation nor in the treatment.

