### Implementation

Random masking will be implemented through the double-blind design. When the patients are allocated, random numbers will be obtained through the central randomisation system. Researchers and patients will know only the random number to avoid the destruction of random grouping.

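### The three hospitals are neither balanced in the randomisation nor adjusted for in the stated analysis: a cheap loss of precision, not a bias

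*Protocol article*

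**What the plan says.** Sequence generation fixes the method: SAS is used "to generate random numbers with simple randomisation". Concealment mechanism, Implementation and Who will be blinded? describe a central system and a randomisation list ("random numbers will be obtained through the central randomisation system") but name no blocks and no strata. Trial design says that patients "will be randomised (1:1) to the test and control groups". Study setting adds: "The study will be completed at three research centres". The expected size of each centre is not given.

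Sample size states that "the sample size is calculated as 47" per group, then: "Considering a loss to follow-up of 10%, the sample size for each group is 52 cases, and the total is 104 cases". Its one remark on centre is: "We assume that no difference in efficacy exists among the three centres".

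Statistical methods for primary and secondary outcomes lists Pearson's chi-squared test, t-tests with and without equal variances, repeated-measures analysis of variance and a Wilcoxon two-sample test. None is described as stratified or adjusted. Methods for additional analyses adds a logistic model whose covariates are picked from univariate results; centre is not named.

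**The concern.** Healing time depends on the operation and on wound care afterwards, and both are delivered by different surgeons and staff at three hospitals. If typical healing time differs between hospitals, centre contributes variance that an unadjusted comparison leaves in the error term. With no stratification, the mix of hospitals can also differ between arms by chance.

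The equal-efficacy assumption does not settle this. It says that the benefit of grafting is the same everywhere. Hospitals could share the same benefit and still differ in healing time in both arms, and that second kind of difference is what matters here. At stake is some power, and the ability to answer a critic who asks whether location contributed to the result.

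**Working it through.** **Inputs from the article.** 104 randomised 1:1; 47 evaluable per group; 10% loss; two-sided 5% level; 80% power; 15 versus 25 days, so a difference of 10; three centres.

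**Inputs assumed, because the article gives none.** The SD, the centre sizes, and the share of variance due to centre.

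**1. The plan's own figure.** 47 × 1.10 = 51.7, rounded up to 52, which reproduces the stated number (47 / 0.90 = 52.2 would give 53). The 47 cannot be checked without an SD. The usual formula n = 2σ²(1.960 + 0.842)²/δ² gives 47 when σ = 10 × √(47/2) / 2.802 = 17.3 days. The formula as printed lacks the factor 2 and would need σ = 10 × √47 / 2.802 = 24.5 days. I use 17.3 and show 24.5 as the other end.

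**2. Arm totals.** Under Binomial(104, 0.5), exactly 52:52 occurs in 7.8% of sequences, a difference of 10 or more in 37.8%, and a smaller arm below 47 before any loss in 28.1%. Power depends on 2·n₁n₂/(n₁+n₂), not on the smaller arm:
- 47:57 is equivalent to 2 × 47 × 57 / 104 = 51.5 per group.
- 42:62 is equivalent to 2 × 42 × 62 / 104 = 50.1 per group.

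With 94 evaluable in the same ratio, power is 80.0% at 52:52, 79.6% at 47:57 and 78.5% at 42:62. Averaged over all splits it is 79.6%, a cost of about 0.4 points.

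**3. Balance within centres.** In a centre of 35, a split of 60:40 or worse occurs in 31% of sequences; in a centre of 20, in 50%. The chance that at least one of the three centres is split that badly is 63% with sizes 35/35/34, and 61% to 78% over the four size patterns tried (35/35/34, 52/26/26, 64/20/20, 70/17/17). The largest centre's share of the two arms differs by 10 points or more in 27% to 30% of trials, and by 20 points or more in 3% to 4%. For scale: if that centre healed 5 days slower than the others (assumed), a 10-point gap would shift the group difference by 0.10 × 5 = 0.5 days, and a 20-point gap by 1 day, against a target of 10.

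**4. Power, by normal approximation.** If centre explains a share s of the variance and is fully removed, SE = SD × √(1 − s) × √(4/104) and power = Φ(10/SE − 1.96).
- SD 17.3: SE is 3.39, 3.22 and 3.03 days at s = 0, 10% and 20%; power is 84%, 87% and 91%.
- SD 24.5: SE is 4.80, 4.56 and 4.30 days; power is 55%, 59% and 64%.

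**5. Which change produces the gain.** Simulation, 8,000 trials per row: centres 35/35/34, difference 10 days, SD 17.3, normal errors, equally spaced centre effects, no loss, stratified blocks of 4 or 6. Simulation error is about half a point.

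| Centre share of variance | Simple, unadjusted | Simple, centre term | Stratified, unadjusted | Stratified, centre term |
|---|---|---|---|---|
| 0% | 83% | 82% | 83% | 83% |
| 5% | 82% | 83% | 83% | 84% |
| 10% | 83% | 86% | 84% | 87% |
| 20% | 83% | 90% | 86% | 90% |

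At shares of 10% and above, most of the gain comes from the centre term. Once it is in the model, stratifying adds 0 to 2 points.

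**The case against.** The case on the other side is strong, and much of it stands.

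- A reader might infer that simple randomisation contradicts the promised 1:1 ratio and 52 per group, or that unequal arms will miss the 47 evaluable per group. The article does not support either reading. 1:1 is met as an allocation probability, 52 is a planning target, and step 2 shows that unequal totals cost almost nothing.
- A reader might also infer that centre biases the comparison. It does not. Simple randomisation gives no systematic bias and keeps the type I error, and the standard error already allows for chance imbalance.
- Covariates in the primary model are often left to the statistical analysis plan, which is not shown and may include centre. That limits the analysis half of the point. It does not reach the allocation method, which the article states and an analysis plan cannot change.
- The population is narrow (a single tract, 5 to 7 o'clock, age 18 to 60, BMI below 30), and one procedure with common aftercare is described. The centre share of variance could therefore be small, and at 5% there is little to gain.
- One unblocked central list is hard to predict. That has value where the operating surgeon necessarily learns the procedure.
- The Trial status section has recruitment starting on 25 March 2021 and completion expected by 24 October 2022, so allocation is probably finished.

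What remains is that the article's stated choices take no account of centre at either stage, and that the analysis half can still be remedied at almost no cost.

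**Conclusion.** The point holds as a worthwhile, inexpensive improvement, not as an error in the plan. With an SD of 17.3 days, a 10-day difference and 104 analysed, a centre term is worth about 3 power points at a 10% centre share, about 7 at 20%, and 2 or fewer at 5%. Stratified randomisation adds 0 to 2 points more. Its main value is credibility, because under simple randomisation some centre is more likely than not to be split 60:40 or worse for every set of centre sizes tried. All of these sizes rest on assumed values for the SD, the centre sizes and the centre share of variance. With an SD of 24.5 days, absolute power is much lower, but the approximate gains are similar (about 4 and 9 points).

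**What to change.** Specify before unblinding that the primary comparison accounts for centre: centre as a covariate for healing time, and a centre-stratified test such as Mantel–Haenszel for the rates. Fix this in advance; do not let centre enter only if a univariate screen selects it. Report arm sizes by centre.

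If any allocation remains, generate it in permuted blocks of varying size, stratified by centre, through the central system already described. For illustration, with blocks of 4 (assumed) the arms could differ by at most 2 within a centre and 6 overall, so the worst split would be 49:55.

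The cost is two degrees of freedom out of about 100, which is within simulation error of no loss even if centre explains nothing. Blocked allocation is slightly more predictable, which varying the block size limits. The planned sample size does not change.

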### Concealment mechanism

Central randomisation will be used. The random and technique numbers will be unified. The randomisation programme will be created by a statistician from the School of Basic Medical Science of GZUCM. The randomly generated number will then be provided in a sealed envelope or online and can be accessed by the clinical trial manager. The participants will be assigned in accordance with the randomly generated number.

### Implementation

Random masking will be implemented through the double-blind design. When the patients are allocated, random numbers will be obtained through the central randomisation system. Researchers and patients will know only the random number to avoid the destruction of random grouping.

## Assignment of interventions: blinding

### Who will be blinded?

A total of 104 eligible subjects will be randomly assigned to two parallel groups. Statisticians will adopt the SAS randomisation programme to generate a randomisation list. Then, the clinical trial manager will divide the patients into two groups in accordance with the randomisation list. All people involved, including the investigators, will be blinded to the assignment of the subjects. The relevant procedures and allocations will be given to the patients by the surgeons in accordance with the randomly generated numbers at different stages. All the study field personnel, patient, sponsor and contract research organisation will remain blinded in the study.

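### The blinding claimed for everyone is impossible for the operating surgeons and doubtful for the wound assessor; the blinding statements need reconciling

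*Protocol article*

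**What the plan says.** Several sections of the protocol article describe blinding, and they differ.

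- Trial design: "This randomised, double-blinded, parallel, superiority trial". Implementation repeats the double-blind label and says that researchers and patients know nothing beyond the random number.
- Who will be blinded?: "All people involved, including the investigators, will be blinded to the assignment of the subjects". The next sentence reads "The relevant procedures and allocations will be given to the patients by the surgeons in accordance with the randomly generated numbers". The one after that reads "All the study field personnel, patient, sponsor and contract research organisation will remain blinded in the study".
- Recruitment: a shorter list, naming assessors and patients as blinded. On follow-up it adds: "These evaluations will be performed by an assistant who will be involved neither in the randomisation nor in the treatment".
- Intervention description: the test arm has a strip of skin freed from the surgical region, prepared as full-thickness skin and stitched into the wound with 4–0 Vicryl. The control arm has fistulotomy only.
- Primary outcomes: cure requires both survival of the grafted skin and complete epithelisation. Exudation is rated by how often underwear or pads are changed in a day.

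**The concern.** A surgeon who performs one of two different operations knows which one it was, so the blinding section contradicts itself from one sentence to the next. The assessor's position is also weak. The wound holds a stitched graft in one arm only, and the cure definition asks whether that graft has survived.

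Healing time, cure within 14 days and total cure all depend on someone judging a wound by eye. Exudation and pain on the Visual Analogue Scale depend on the patient. Readers will give these outcomes more weight if they believe that everyone was blinded. If the label is wrong, the trial claims a protection against bias that it has only in part.

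**Working it through.** This is mainly a check of consistency, so the statements are taken by role.

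1. **Operating surgeons.** The blinding section includes investigators and all field personnel among the blinded, yet it has the surgeons give the allocated procedure. The two procedures differ in harvesting, preparing and suturing a 1.0 cm × 3.0 cm strip of skin. Blinding is impossible for this role. Implementation cannot hold for the surgeons either, since the random number must lead them to an operation.
2. **Wound assessor.** Recruitment says that assessors are blinded and gives the evaluations to an assistant outside randomisation and treatment. That separates the assessor from the allocation list and the operating room. It does not hide the wound. To apply the cure definition as written, the assessor must look for a graft, and control wounds have none. Blinding is doubtful here. That the graft can be seen is inferred from the surgical description and the cure definition, because the figures are not available.
3. **Patients.** The article says that they are not told their arm. Spinal anaesthesia, a graft taken from the wound area itself and otherwise identical aftercare make blinding plausible. No step to protect it is described, and the surgeons know the arm. Patient blinding is unsupported, not disproved.
4. **Agreement between sections.** Recruitment names a subset of the roles listed in the blinding section. That is narrower and not in itself a contradiction. The contradiction lies between the claim for all people involved and the surgeons' role.

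**Scale, as an illustration only.** The documents give no size for any reading bias, so the share *f* below is assumed. Inputs from the article: planned mean healing times of 25 and 15 days (Sample size), a difference of 25 − 15 = 10 days; visits on days 14 and 21 (Recruitment), 21 − 14 = 7 days apart; 52 patients per arm. Suppose that a share *f* of test patients is read as healed one visit early.

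- Shift in the mean = *f* × 7 days. For *f* = 20%: 0.20 × 7 = 1.4 days. For *f* = 50%: 0.50 × 7 = 3.5 days. Both are well below 10.
- Cure within 14 days would rise by *f* itself, 20 or 50 percentage points, but only if every shifted patient moves from the day-21 to the day-14 reading.
- With no true difference, moving 10 of 52 test patients (10/52 = 19.2%) to cured gives a Pearson chi-squared of d² × 52 / [2p(1 − p)], where d = 10/52 and p is the pooled rate. Since p(1 − p) is at most 0.25, the statistic is at least 0.03698 × 52 / 0.5 = 3.846, which is P < 0.05 whatever the control rate.

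Under these assumptions the planned difference in mean healing time is fairly robust to such a bias, and the 14-day cure rate is much less so.

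**The case against.** The strongest reply is that the plan does protect its outcomes: the evaluating assistant is independent of both randomisation and treatment. That stands, and a reader who inferred that nothing replaces the missing blinding would be wrong. The protection is partial because the wound itself is not masked.

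Other stronger readings are tempting but go beyond the text.

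- *The random number reveals the arm.* The sentence "The random and technique numbers will be unified" is ambiguous. A shared number need not disclose the arm to someone without the list.
- *Patients are unblinded.* The article does not show this, for the reasons given under the patients' role above.
- *Unblinded surgeons decide discharge and withdrawal.* No section says who decides discharge. Withdrawal rests with investigators or the subject, not expressly with the operating surgeon. Nor is it stated how days to return to work are collected.
- *The bias has a known size.* The 20% and 50% shares, the one-way shift and the premise that healing is dated only at visits are all assumptions.

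Timing also limits what can change. The article was published in July 2023, and its Trial status section expected completion by 24 October 2022. Statements about blinding and supportive analyses can still be corrected at reporting; the way wounds were examined may already be settled.

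**Conclusion.** The concern holds in a limited form. As written, the double-blind label and the claim that everyone is blinded are false for the operating surgeons. This follows from the article's own text and needs no assumption. For the wound assessor, blinding is doubtful, which rests on the inference that a stitched graft can be recognised. For patients, it is asserted without a described safeguard.

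No figure in the documents measures the consequence, and the illustration is not evidence that biased reading occurs. What changes is the claim the trial can make: its visually judged primary outcomes come from an independent assessor whose masking is uncertain, and its patient-dependent outcomes rest on blinding that has not been secured.

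**What to change.** Reconcile Trial design, Recruitment, Implementation and Who will be blinded? so that they give one account:

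- drop the double-blind label and the claim covering all people involved;
- state that operating surgeons are unblinded;
- state that an independent assistant evaluates outcomes without operative notes or allocation, but may recognise a graft;
- state that patients are not told their arm.

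Define healing as complete epithelisation, applied in the same way to both arms, so that the definition does not itself send the assessor looking for a graft. Graft survival can be reported separately in the test arm.

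As a supportive sensitivity analysis, have the available wound photographs read under code and in random order. This should not replace the primary healing date. Photographs are taken only with the patient's agreement, so some will be missing; a graft may be recognisable in them; and if the follow-up assistant reads them, coding may not mask that person. Interpret the visually judged and patient-dependent outcomes with this limit on blinding stated.

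The cost is loss of the double-blind label, some reading time, and a sensitivity analysis that is incomplete for patients who decline photographs.

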### Procedure for unblinding if needed

Unblinding meetings will be held. Unblinding in emergency situations will also be implemented through the central randomisation system.

## Data collection and management

### Plans for the assessment and collection of outcomes

A CRF will be used to assess and collect outcomes and baseline information. In addition, the clinical trial database will be constructed by a designated data manager who will be responsible for regular database management and maintenance. All data will be imported into the clinical trial database by two research assistants. The investigator will be responsible for maintaining accurate, complete and up-to-date records for each subject. The investigator will also be responsible for maintaining any source documentation related to the study, including any films, tracings, computer discs or tapes.

The anonymity of the participating subjects will be maintained. For data collection and management purposes, the subjects will only be identified by subject numbers. Documents that identify the subject beyond the subject number will not be submitted to the sponsor (e.g. the signed informed consent document and subject initials) and will be maintained in strict confidence by the investigator except to the extent necessary to allow auditing by regulatory authorities, study monitor or sponsor representatives.

Field personnel will record all data for each study subject on electronic CRFs (eCRFs) by using an electronic data capture (EDC) system. A study procedure manual for additional information regarding CRFs will be used as source documentation. The eCRFs will be completed on-site in a timely manner, and the investigator will promptly review the completed eCRFs for each subject after every visit. As the person is ultimately responsible for the accuracy of all eCRF data, the investigator will sign the Investigator’s Statement in each subject’s eCRF.

### Plans to promote participant retention and complete follow-up

Follow-up will be conducted at baseline, at 1 week ± 3 days, 2 weeks ± 3 days, 3 weeks ± 3 days, 4 weeks ± 3 days, 8 weeks ± 3 days and 12 weeks ± 3 days and 24 weeks ± 3 days. Any missing or incorrect data will be detected by the software system. In such a case, the original CRFS will be checked to correct or complete every piece of data.

